# A hybrid digital parenting programme to prevent abuse of adolescents in Tanzania: statistical analysis plan for a pragmatic cluster randomised controlled trial

**DOI:** 10.1186/s13063-024-08292-6

**Published:** 2024-07-03

**Keywords:** Child abuse, Parenting, Adolescents, Digital, Low- and middle-income countries, Violence against children

## Abstract

**Background:**

Globally, violence against children poses substantial health and economic challenges, with estimated costs nearing USD 7 trillion. This prompts the urgent call for effective evidence-based interventions in preventing and mitigating violence against children. ParentApp is a mobile, open-source application designed to offer a remote version of the Parenting for Lifelong Health (PLH) programme. ParentApp is the first digital parenting intervention for caregivers of adolescents aged 10–17 years to be tested in low- and middle-income settings.

**Methods:**

This study is a pragmatic, two-arm, cluster-randomised trial in Mwanza, Tanzania’s urban and peri-urban areas. Assessments are set for baseline, 1 month post-intervention, and 12 months post-intervention. We randomised 80 clusters, each with about 30 caregiver-adolescent dyads, with a 1:1 ratio stratified by urban or peri-urban location. Both arms receive an entry-level smartphone preloaded with Kiswahili apps—ParentApp for intervention and WashApp control.

The primary method of analysis will be generalised linear mixed-effects models with adjustment for person-level characteristics and multiple imputation. In three-level models, measurement waves are nested within a person, nested within a sub-ward. Regressions will constrain groups to be equal at baseline and include covariates for stratification, percentage of male caregivers, and individual-level characteristics.

**Discussions:**

Preparations for the trial began in December 2022, including community mobilisation and sensitisation. Rolling recruitment, baseline data collection, and implementation onboarding took place between April and September 2023. One-month post-test data collection began in August 2023 and thus far achieved 97% and 94% retention rates for caregivers and adolescents respectively. Final post-test data collection will begin in September 2024, anticipated to run until April 2025. This SAP was submitted to the journal before the interim analysis to preserve scientific integrity under a superiority hypothesis testing framework.

**Trial registration:**

The trial was registered on the Open Science Framework on 14 March 2023: https://doi.org/10.17605/OSF.IO/T9FXZ.

The trial protocol was published in Trials 25, 119 (2024): [name], [name], [name] et al. A hybrid digital parenting programme to prevent abuse of adolescents in Tanzania: study protocol for a pragmatic cluster-randomised controlled trial. Trials 25, 119 (2024). https://doi.org/10.1186/s13063-023-07893-x.

## Introduction

### Background and rationale (7)

Violence against children is estimated to affect over a billion children a year [1]. Instances of violence adversely affect communities in low- and middle-income countries with the African continent experiencing one of the highest rates of verbal, physical, and sexual violence among children and adolescents [2, 3]. The repercussions of violence against children span multiple adverse and often long-term outcomes across the lifecycle and can lead to increased demands on health and welfare systems [4–6]. Global estimates of the cost of violence against children is nearly USD 7 trillion [7], resulting in an international commitment to ending violence against children as a strategic objective for sustainable development [8].

Parenting programmes have emerged as a cornerstone strategy in preventing and reducing violence against children, with evidence-based interventions demonstrating significant benefits in improving parenting practices and child outcomes [9]. However, the scale up of these programmes can be challenging and costly. In the wake of the COVID-19 pandemic, there is a global shift toward digital interventions through hybrid and remote mobile app design. The digital delivery of parenting programmes presents a viable solution to these challenges, potentially offering greater reach and accessibility in settings experiencing rapid increases in smartphone penetration [10]. Digital or hybrid digital interventions, which combine remote or in-person human support with digital delivery, may be a valuable delivery approach to increase the scale-up of parenting programmes at national levels. A systematic review identified 15 randomised trials of digital parenting programmes with promising results; however, these are concentrated in the Global North and target parenting of younger children. Few studies have looked at digital interventions for parenting adolescents in the Global South [11].

ParentApp for Teens (referred to hereafter as ParentApp) is a mobile application designed to offer a remote version of the Parenting for Lifelong Health (PLH) programme; PLH is an open-source, evidence-based intervention, tailored for families in LMICs, showing promise in reducing violence against children, enhancing positive parenting, and improving family financial management [12, 13]. ParentApp is the first digital parenting intervention for caregivers of adolescents aged 10–17 years to be tested in low- and middle-income settings. The app, designed specifically for contexts with limited to no internet, was developed between 2019 and 2022 through a seven-stage process that involved multi-phased co-development with various stakeholders, participatory engagement across 14 African countries, mixed-methods user testing, a feasibility pilot, a pre-post pilot, a cluster-randomised optimisation factorial trial, and two qualitative studies included in the feasibility pilot and optimisation trial. The adaptation and optimisation of ParentApp was conducted in partnership with the Universities of Oxford and Cape Town, IDEMS International, Tanzania’s National Institute for Medical Research (NIMR), Parenting for Lifelong Health, and Clowns Without Borders South Africa (CWBSA), with support from the Tanzania-based NGO Investing in Children and Strengthening their Societies (ICS) and extensive collaborations with researchers, programme specialists, technical experts, caregivers, and adolescents.

This trial aims to rigorously evaluate the effectiveness and cost-effectiveness of ParentApp in reducing maltreatment and sexual violence risks among adolescents aged 10–17 years through digital parenting programme delivery in urban and peri-urban communities. The trial is set in Mwanza, Tanzania, where the in-person PLH programme has been successfully delivered, and the scale-up of parenting programmes is a national commitment [14].

This paper presents the statistical analysis plan (SAP) of the ParentApp Randomised Controlled Trial, building upon the existing study protocol [15].

### Objectives (8)

The SAP is guided by the trial objectives, informing the choice of statistical methods, the handling of data, and the interpretation of results. The trial has the following objectives:Determine the effectiveness of the ParentApp intervention by assessing if the intervention, compared to a control condition (WashApp), effectively decreases rates of adolescent maltreatment (physical and emotional abuse) and sexual violence victimisation and vulnerability at 1 month and 12 months post-interventionEvaluate cost-effectiveness by analysing the economic viability of the ParentApp intervention by analysing its cost-effectiveness in achieving the primary and secondary outcomes, from a perspective that encompasses the public and health sector, and participant costs and benefitsAssess scalability and delivery by investigating the feasibility of delivering ParentApp at scale through local implementing partners, focusing on the programme’s accessibility and participant engagement within the Tanzanian contextExplore possible mechanisms of change through mediation and moderation analyses. To identify pathways through which ParentApp impacts behavioural outcomes, including changes in parenting practices, adolescent behaviour, and family dynamics

## Study methods

### Trial design (9)

The design of this study is a pragmatic, two-arm, cluster-randomised controlled trial (RCT) within the urban and peri-urban settings of Mwanza, Tanzania. The study’s assessments will be collected at baseline, followed by evaluations at 1 month post intervention and at 12 months post intervention. The trial encompasses the randomisation of 80 urban and peri-urban clusters, each consisting of approximately 30 caregiver-adolescent dyads. Randomisation will follow a structured design and be conducted at the cluster level, adhering to a strict 1:1 allocation ratio.

Caregivers in both the intervention arm and control arm will be provided with an entry level, locally sold, smartphone; phones will be preloaded with the Kiswahili version of ParentApp for the intervention arm and a simple hygiene programme, WASH App, for the control arm. The intervention group will also be added to facilitated WhatsApp groups for the exchange of insights and learnings among caregivers.

### Randomisation (10)

To increase community and participant acceptance of the outcome, a participatory randomisation approach will be used. This involves representatives from the selected communities drawing a number that corresponds to a concealed randomisation sequence. Clusters will be randomly assigned to either the control or intervention group with a 1:1 allocation in blocks of six stratified by urban vs peri-urban context. The implementing partner will notify the participating families of their allocation status after baseline data collection in their cluster is complete to ensure that participants are blind to allocation during the pre-test assessment. While participants will not be blind to their own treatment condition, the allocation status of participating families in other sites/clusters will be concealed, thus reducing the potential for contamination. Blinding will not be possible for facilitators and local research staff due to their involvement in programme implementation.

### Sample size (11)

The sample size is based on a detailed power calculation informed by preliminary pilot study data, using generalised Poisson linear mixed-effect models. These calculations posit that, to achieve a statistical power of 80% against an anticipated effect size of 0.95 and a control group mean outcome of 4, while accounting for potential attrition rates within both the control and intervention arms, a minimum ensemble of 80 clusters, each comprising 30 dyads, is required. The trial will therefore enrol a cohort of approximately 2400 caregiver-adolescent dyads or 4800 participants.

A subset of participants, comprising 40 to 60 caregivers and 20 to 30 adolescents, will be invited to engage in post-intervention qualitative interviews. These discussions are aimed at eliciting in-depth insights into the experiential dimensions of the programme, thereby enriching the quantitative data. Additionally, semi-structured interviews will be conducted with a representative sample of 10 implementing staff members, offering a comprehensive perspective on programme delivery dynamics.

Expanding the impact of the study, we intend to include adolescent siblings or co-resident adolescents present within approximately 50% of the participating households (estimated *n* = 2610) in the post-intervention assessment phase. This strategic inclusion aims to ascertain the broader familial impact of the intervention, thereby capturing any auxiliary effects on the household’s adolescent population not directly involved in the primary intervention activities.

### Framework (12)

Statistical analyses within this study will be conducted under the control of a superiority hypothesis testing framework. This approach has been selected to ascertain whether the intervention exhibits a statistically significant and clinically meaningful impact over the control condition.

### Statistical interim analyses and stopping guidance (13a, b, c)

Interim analyses will be conducted at 1 month post-intervention (4 months post-baseline). During the interim analysis, the nominal significance has been set at *p* < 0.001 to mitigate the risk of type I error or false-positive findings due to multiple testing across the trial’s timeframe. The residual nominal significance level for the final analyses will thus approximate *p* = 0.05. As such, while 95% confidence intervals will be calculated to facilitate the interpretation of the interim results, these results will not be used to make conclusive statements about the intervention’s effectiveness.

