## Statistical principles

### Confidence intervals and p values (16, 17, 18)

All reported confidence intervals will be at the 95% level. Any hypothesis testing will be undertaken at the level of statistical significance corresponding to the prespecified alpha level of *α* = 0.05 with two-tailed tests for all analyses. Minimal clinically important differences are not well understood or established for many outcomes included in this analysis. Therefore, we will not explicitly benchmark findings against these differences in any primary analyses.

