The intervention’s effectiveness will be evaluated through multiparameter Wald tests or likelihood ratio tests as appropriate, comparing models with and without intervention-by-time interactions to assess the totality of the intervention’s impact. Furthermore, the use of Wald tests will assess the significance of specific fixed effects model coefficients, particularly in relation to the intervention-by-time interactions. In addition to the primary analysis, we will conduct both adjusted analyses with unimputed data and unadjusted analyses with unimputed data, which include terms for stratification, time, and intervention-by-time, to provide a baseline estimate of intervention effectiveness without covariate adjustments.

Both Wald tests and marginal effects plots will be used to evaluate differences of outcome interactions by intervention group and will be supported by the computation of intra-cluster correlation coefficient (ICC) for hierarchical data. Depending on the distribution of the data, i.e. binary or Poisson, median incidence rate ratios (IRR) or odds ratios for hierarchical and non-normally distributed data will be respectively calculated.

The *p*-value threshold will be 0.05 for all pre-specified analyses. However, due to multiple comparisons planned for exploratory analyses, a sharpened *q*-value will be used with respect to all exploratory analyses to adjust the *p*-value threshold for statistical significance to reduce the likelihood of false positives.

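### The 0.001 interim threshold does not control false positives across waves, because the final model tests the 1-month effect again at 0.05 beside the 12-month and joint tests, with no stated order

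*Protocol article*

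**What the plan says.** The section on statistical interim analyses and stopping guidance places an interim analysis at the 1-month follow-up. It fixes the threshold ("During the interim analysis, the nominal significance has been set at *p* < 0.001") and gives the purpose: "to mitigate the risk of type I error or false-positive findings due to multiple testing" during the trial. It then draws a consequence: "The residual nominal significance level for the final analyses will thus approximate *p* = 0.05". It adds that "these results will not be used to make conclusive statements about the intervention’s effectiveness".

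Other sections bear on the same 1-month effect:

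- **Objectives:** the first objective asks whether the intervention reduces maltreatment and sexual violence at both 1 month and 12 months. No time point is named as primary.
- **Timing of final analysis:** the final analysis follows database lock, after all data collection, so it contains the 1-month data.
- **Analysis methods for primary and secondary outcomes:** one model covers all waves, with arms constrained equal at baseline. The intervention-by-time interactions are the test of effectiveness. A multiparameter Wald or likelihood ratio test takes both interactions together. In addition, "the use of Wald tests will assess the significance of specific fixed effects model coefficients", with those interactions singled out. The "threshold will be 0.05 for all pre-specified analyses". Only exploratory analyses receive an adjustment (sharpened q-values).
- **Confidence intervals and p values:** a two-sided 0.05 level applies to any hypothesis test, with no exception for the interim.

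**The concern.** This interim is not an early look at accumulating 12-month data. It analyses the 1-month wave, which is an endpoint in its own right under the first objective, and the final model estimates the same effect again. A strict threshold at a first look protects a conclusion only if that conclusion is not reopened later at a looser one. Here the 1-month effect is held to 0.001 in the interim report and can then be claimed at 0.05 in the final report. The 12-month effect and the joint test are also each available at 0.05.

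The plan offers the 0.001 rule as its safeguard against multiple testing over time. A reader of the final paper could therefore take either wave-specific p-value below 0.05 as a finding made at an overall 5% level for that outcome. As written, the rules do not deliver that level.

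**Working it through.** **Inputs from the article.** Interim level 0.001; overall two-sided level 0.05; two post-baseline interactions (1 and 12 months); one joint test with 2 degrees of freedom; 0.05 for each pre-specified test; no stated gate.

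**Assumption.** The correlation ρ between the 1-month and 12-month test statistics is not given. Both estimates share participants, clusters and the constrained baseline, so a positive value is likely. A range of 0.2 to 0.9 is shown, with 0 as a reference.

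**Step 1: the plan's own figure.** Level left for a single final test after a look at 0.001:

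- additive: 0.05 − 0.001 = 0.0490
- Šidák: 1 − 0.95/0.999 = 0.04905
- bivariate normal, solving P(reject at interim or final) = 0.05: 0.0491 at ρ = 0.2, 0.0494 at ρ = 0.5, 0.0500 at ρ = 0.9

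All of these round to the stated 0.05. Spending 0.001 and then a full 0.05 costs at most 0.001 + 0.05 = 0.051. The plan's figure reproduces for one final test.

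**Step 2: what the final model tests.** Let Z₁ and Z₁₂ be the two interaction statistics, standard normal under the global null with correlation ρ.

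- Either wave at 0.05: 1 − P(|Z₁| < 1.96 and |Z₁₂| < 1.96). At ρ = 0 this is 1 − 0.95² = 0.0975.
- Joint test: W = (Z₁² − 2ρZ₁Z₁₂ + Z₁₂²)/(1 − ρ²), rejecting when W exceeds the 95% point of chi-squared on 2 df, −2 ln 0.05 = 5.99.

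Probability of at least one false claim, per outcome and informant (4 million simulated draws per row; the wave-test column agrees with the bivariate normal calculation):

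| ρ | either wave at 0.05 | either wave or joint test | 1 month only at 0.001, 12 months at 0.05 | wave claim only after joint test rejects |
|---|---|---|---|---|
| 0 | 9.7% | 10.0% | 5.1% | 4.7% |
| 0.2 | 9.6% | 10.0% | 5.1% | 4.6% |
| 0.3 | 9.5% | 10.0% | 5.1% | 4.5% |
| 0.5 | 9.1% | 9.9% | 5.1% | 4.2% |
| 0.7 | 8.4% | 9.6% | 5.0% | 3.7% |
| 0.9 | 7.0% | 8.8% | 5.0% | 3.2% |

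**Step 3: what the interim look contributes.** If the final 1-month statistic is essentially the interim one, any rejection at 0.001 is also a rejection at 0.05. Adding the interim look therefore leaves the second column unchanged (9.74% with and without it at ρ = 0). The excess over 5% comes from the parallel tests in the final model, not from the interim.

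**Step 4: why a gate works.** There are two elementary hypotheses (no effect at 1 month, no effect at 12 months) and one intersection, which the joint test addresses. Rejecting an elementary hypothesis only when both its own test and the joint test reject at 0.05 is the closed testing procedure. If both nulls are true, a wave claim requires the joint test to reject, so the error is at most 5%. If only one is true, the error is at most the 5% of its own test.

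**The case against.** The strongest reply is that the plan already has a sensible order. The multiparameter test is named first, as the assessment of the overall impact, and the coefficient tests follow as a supplement. Read that way, effectiveness rests on one 5% test per outcome. The reply has weight: joint test first is a natural reading, and it makes counting the joint test as a separate third route the less favourable interpretation. But the article states no gate, gives every pre-specified test 0.05, and sets both time points as objectives, so nothing bars a wave-specific claim when the joint test fails.

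A second reply is that the interim is declared non-conclusive, so 0.001 followed by 0.05 is a sequence and not a contradiction. This also stands in part. The disclaimer and the strict threshold do restrain claims made at the interim. They do not extend to the final 1-month coefficient.

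Several stronger readings are tempting, and the article does not support them:

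- **That the statement about 0.05 remaining is false.** It is correct for a single final test.
- **That the error rate is simply 10%.** That is the upper end. It needs independent or weakly correlated waves with the joint test counted as a separate route, and the correlation is an assumption.
- **That a 1-month p of 0.03 would be declared both ineffective and effective.** The interim makes no conclusive declaration.
- **That the interim intervals are wrong because 95% does not match 0.001.** They are meant to aid interpretation of provisional results, and "All reported confidence intervals will be at the 95% level" is a uniform rule that 99.9% intervals would break.
- **That the mediation analysis is compromised.** It also requires a 12-month effect, and its final plan is to be lodged on the Open Science Framework before it is run.

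**Conclusion.** The concern holds in a limited form. The level quoted for the final analyses is right for one test, but the control over time that the 0.001 rule is meant to provide is not achieved. The final model reopens the 1-month effect at 0.05 beside two other 0.05 tests with no hierarchy. Under the global null, two ungated wave tests give about 9.6% false positives at ρ = 0.2, falling to 7.0% at ρ = 0.9. With the joint test as a third route the figures are about 10.0% to 8.8%. The plan implies about 5%.

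These figures assume approximately normal test statistics, the stated correlation range and ungated wave tests. They are per outcome and informant; multiplicity over several primary outcomes is a separate matter. If the joint test was always meant to come first, the plan needs only to say so. This should be fixed, but it does not threaten the trial design.

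**What to change.** In the analysis methods section, state for each primary outcome that the joint intervention-by-time test at 0.05 is the gate, and that the 1-month and 12-month coefficients are interpreted at 0.05 only if it rejects. No alpha needs to be split.

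Bring three sections into line: the interim analyses section, the section on confidence intervals and p values, and the threshold sentence in the analysis methods. Each should say that 0.001 applies only to the interim report and that the final 1-month conclusion comes from the gated test. The 95% intervals can stay.

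Naming 12 months as the sole primary time point would also control the error, but it would demote half of the first objective, so it is more than a wording change.

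The cost of the gate is that a wave-specific p below 0.05 cannot be claimed when the joint test does not reject, which matters most if the effect is confined to one wave. No data, sample size or model changes. The article reports that 12-month data collection had yet to start, so at that stage the order could be fixed before those data existed.
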